### Sample size calculation

Based on the results from the DARWIN1, DARWIN2, and FINCH3 trials, this study assumes a mean difference in change from baseline in DAS28-CRP at week 24 between the two groups of 0.07, with a standard deviation of 1.1. With an equal sample size ratio of 1:1 between the groups, and assuming a mean difference of 0.07, a standard deviation of 1.1, a one-sided significance level of 0.05, and a power of 80%, the required sample size was calculated to be 108 participants (54 per group). As for the sample size calculation, a one-sided test was employed based on the clinical assumption that filgotinib monotherapy would not be inferior to the combination of filgotinib and MTX. Considering a dropout rate of approximately 10%, the total sample size was set at 120 participants (60 per group).

### Trial treatments

#### Details of the study treatment.

Subjects who meet the inclusion criteria above and do not meet any exclusion criteria will initiate either a combination therapy with filgotinib 200 mg/day (or 100 mg/day if estimated glomerular filtration rate is below 60 mL/min/1.73 m²) and MTX (Add-on group) or filgotinib monotherapy (Switch group) after completing the baseline assessment (week 0). bDMARDs and csDMARDs other than MTX must be discontinued at the start of filgotinib administration. In the Add-on group, MTX should be maintained at the same dose as at enrollment until week 24 unless clinically significant adverse events occur. After week 24, patients in the Add-on group may reduce or discontinue MTX, while patients in the Switch group may resume MTX administration if desired by the patient and agreed upon by the attending rheumatologist.

#### Concomitant medications.

**
*Permitted concomitant therapies*
**

The use of oral glucocorticoids (≤10 mg/day in prednisolone equivalents), oral or suppository nonsteroidal anti-inflammatory drugs, and topical medications (skin ointments, eye drops, nasal sprays, inhaled medications) is permitted. Intravenous administration of glucocorticoids at a dose equivalent to ≤10 mg/day of prednisolone, or intra-articular injection of triamcinolone acetonide 40 mg, may be temporarily prescribed if oral administration is difficult or for other reasons. Additionally, glucocorticoid use for indications other than rheumatoid arthritis is permitted without dose restrictions, but only for a duration of up to 2 weeks.

#### Prohibited and restricted concomitant therapies.

Use of csDMARDs other than MTX, JAK inhibitors other than filgotinib, or bDMARDs is prohibited from the start of filgotinib administration until the end of the study treatment. Administration of live vaccines is also prohibited. For medications listed as requiring caution in the package insert (itraconazole, rifampin, famotidine, omeprazole, midazolam, metformin, ethinylestradiol, levonorgestrel, pravastatin, rosuvastatin, and atorvastatin), their use is permitted but should be conducted with careful monitoring of the patient’s condition.

### Outcomes

#### Primary endpoint.

The primary endpoint is the change in DAS28-CRP from baseline at week 24, with the objective of determining if the Switch group is non-inferior to the Add-on group. The non-inferiority margin of 0.6 was adopted based on the study by Rubbert-Roth et al [12]. The value of 0.6 was derived by Rubbert-Roth and colleagues based on the meta-analysis results of treatment effects using DAS28 in patients with rheumatoid arthritis, as well as the fact that a change of 0.6 or less is internationally adopted in the EULAR response criteria as a threshold indicating no clinically significant change [13].

#### Secondary endpoints.

1) Remission achievement rate

The rate of achieving remission at each time point based on DAS28-CRP, Simplified Disease Activity Index (SDAI), Clinical Disease Activity Index (CDAI), and Boolean criteria will be analyzed. The denominator for the proportion will be the number of full analysis set (FAS) in each group, and subjects who discontinue early will be considered as non-achievers. The definition of remission is as follows: DAS28-CRP < 2.6, SDAI ≤3.3, CDAI ≤2.8, Boolean criteria with ≤1 for all of the following items: tender joint count, swollen joint count, patient visual analog scale (VAS), and CRP.

2) Low disease activity achievement rate

The rate of achieving low disease activity at each time point based on DAS28-CRP, SDAI, and CDAI will be analyzed. The denominator for the proportion will be the number of FAS in each group, and subjects who discontinue early will be considered as non-achievers. The definition of achieving low disease activity is as follows: DAS28-CRP ≤ 3.2, SDAI≤11, and CDAI≤10.

3) Change from baseline in DAS28-CRP, SDAI, and CDAI

Change from baseline in DAS28-CRP, SDAI, and CDAI at each time point will be analyzed.

4) ACR20/50/70 and ACR-N achievement rates

Achievement rates of ACR20, ACR50, and ACR70, as well as ACR-N at each time point, will be analyzed. For ACR20, ACR50, and ACR70, the denominator for the proportion will be the number of FAS in each group, and subjects who discontinue early will be considered as non-achievers.

5) Functional remission achievement rate

The rate of achieving functional remission in Health Assessment Questionnaire (HAQ) at each time point will be analyzed. The denominator for the proportion will be the number of FAS in each group, and subjects who discontinue early will be considered as non-achievers. Functional remission is defined as HAQ ≤ 0.5.

6) Structural remission achievement rate

The rate of achieving structural remission in modified Total Sharp Score (mTSS) at week 24 and week 48 will be analyzed. The denominator for the proportion will be the number of FAS in each group, and subjects who discontinue early will be considered as non-achievers. Structural remission at both week 24 and week 48 is defined as an mTSS progression of ≤0.5.

7) Clinical relevant radiographic progression (CRRP, ΔmTSS ≥3) and rapid radiographic progression (RRP, ΔmTSS ≥5) rates

The rate of CRRP and RRP at week 24 and week 48 will be analyzed. The denominator for the proportion will be the number of FAS in each group, with the numerator for the CRRP rate being the number of cases with an mTSS increase of 3 or more at week 24 and 48, and the numerator for the RRP rate being the number of cases with an mTSS increase of 5 or more at week 24 and 48.

8) Cumulative values of CRP and matrix metalloproteinase (MMP)-3

The cumulative values of CRP and MMP-3 will be analyzed, with definition as the area under the curve (AUC) for CRP and MMP-3 for each subject.

9) Work productivity and activity impairment (WPAI)

WPAI at week 24 and week 48 will be analyzed. At week 24, summary statistics will be calculated for baseline values, measurements at each time point (week 24 and week 48), and changes from baseline in the two groups (Add-on group and Switch group). At week 48, the analysis will include four groups (Add-on to Switch group and Switch to Add-on group in addition to the original two groups).

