#### Full analysis set (FAS).

All subjects who have received the study drug (filgotinib) and have valid efficacy data with at least one measurable point will be included in the FAS, which will be used for efficacy analysis.

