For the safety analysis, treatment-emergent adverse events (TEAEs) observed during the period from the start of the study treatment to the end of the observation period will be summarized. Adverse events that cannot be ruled out as being causally related to the study treatment will be classified as adverse drug reactions. For each group, the number and percentage of cases of TEAEs and adverse drug reactions will be summarized by system organ class and preferred term. Additionally, a summary by severity level will also be provided.

Missing data at each time point will not be imputed. For patients who discontinue the study, only the data obtained up to the point of discontinuation will be used for analysis. Additionally, when analyzing the proportion of patients who achieve the endpoint, cases with missing data at each time point, including those who discontinued the study, will be considered as non-responders and included in the denominator.

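### CRRP and RRP score patients without a film as non-progressors: progression is modestly understated, and an arm is favoured only if missing films are unequal

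*Protocol article*

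**What the plan says.** All references are to the protocol article.

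- **Secondary endpoints, item 7.** The denominator is set first: "The denominator for the proportion will be the number of FAS in each group, with the numerator for the CRRP rate being". What then follows, as the CRRP count, is "the number of cases with an mTSS increase of 3 or more at week 24 and 48". For RRP the numerator is "the number of cases with an mTSS increase of 5 or more at week 24 and 48". Item 7 has no clause on early discontinuation.
- **Full analysis set.** Treated patients who "have valid efficacy data with at least one measurable point will be included in the FAS" belong to it. No follow-up radiograph is needed.
- **Statistical methods, missing data.** "Missing data at each time point will not be imputed", and for proportions "cases with missing data at each time point, including those who discontinued the study, will be considered as non-responders and included in the denominator".
- **Secondary endpoints, item 6.** "Structural remission at both week 24 and week 48 is defined as an mTSS progression" of 0.5 or less. Early discontinuers are scored as not achieving it. Items 1, 2 and 5 carry the same clause, as do the ACR20/50/70 rates in item 4.
- **Fig 1 legend.** Hand and foot films at discontinuation are implied, because they are waived only when the previous film is no more than 28 days old. No section says whether such a film counts at week 24 or week 48.

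**The concern.** Counting a missing patient as a non-responder is conservative when responding is good, as with remission, low disease activity or ACR response. CRRP and RRP are bad outcomes, so failing to meet the endpoint is the favourable result. The same rule then gives a patient with no film the best possible score.

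Two things follow. The progression rates are too low whenever a patient without a film has in fact progressed. And one patient with no film is a failure in item 6 but a good result in item 7, although both items rest on the same radiographs. If the arms lose different proportions of films, items 6 and 7 can point in opposite directions for that reason alone. This matters because the Discussion hopes to support monotherapy as having equivalent efficacy, and CRRP and RRP are the endpoints that count patients with substantial structural damage.

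**Working it through.** **The plan's own figures.** No expected CRRP or RRP rate is stated, and neither endpoint is powered. The relevant planning figures are in Sample size calculation: 108 patients, about 10% dropout, 120 in total (60 per group). They agree: 108 / 0.90 = 120.

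**Inputs**
- From the document: the item 7 numerator and denominator, the missing-data rule, the item 6 rule, about 10% dropout, 60 per group.
- Assumed, because the document gives no values: the true progression rate *p*; the share *m* of FAS patients without a film; true structural remission of 80%; and, except in step 4, missingness unrelated to outcome. Equating the 10% dropout with 10% missing films is also an assumption.

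**Step 1: what the rule reports.** Only patients with films can enter the numerator, so

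reported rate = *p* × (1 − *m*).

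With *p* = 10% and *m* = 10% in both arms: 0.10 × 0.90 = 9.0% in each. Both rates are understated by one tenth of their value, and there is no between-arm bias.

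**Step 2: unequal missingness, equal true rates.** With *p* = 10%, and 5% versus 15% missing (3 versus 9 of 60):
- 0.10 × 0.95 = 9.5%
- 0.10 × 0.85 = 8.5%
- ratio 0.85 / 0.95 = 0.895, in favour of the arm with more missing films

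The false difference is *p* × (*m*₂ − *m*₁):

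| True rate in both arms | 5% vs 15% missing | 5% vs 25% missing |
|---|---|---|
| 5% | 0.5 points | 1.0 points |
| 10% | 1.0 points | 2.0 points |
| 15% | 1.5 points | 3.0 points |
| 20% | 2.0 points | 4.0 points |

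**Step 3: item 6 on the same patients.** With 80% true structural remission in both arms, item 6 reports 0.80 × 0.95 = 76% versus 0.80 × 0.85 = 68%. The arm with more missing films looks worse on item 6 and better on item 7, although the arms do not differ.

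**Step 4: dropouts progress more often.** Suppose completers progress at 10%, dropouts at 30%, and 5% versus 15% are missing.
- True rates: 0.095 + 0.05 × 0.30 = 11.0%, and 0.085 + 0.15 × 0.30 = 13.0%
- Item 7 as written: 9.5% versus 8.5%, so the order is reversed
- Observed cases only: 10% versus 10%, so the reversal goes but the true difference is still missed
- Missing counted as progression: 0.095 + 0.05 = 14.5%, and 0.085 + 0.15 = 23.5%

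**Step 5: scale.** At a rate of 10% with 60 per arm, the 95% confidence interval for a difference has a half-width of about 1.96 × √(2 × 0.10 × 0.90 / 60) = 10.7 points. The 1.0-point distortion in step 2 is 0.6 of a patient in 60.

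**The case against.** The case against giving this much weight is substantial.

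- **The between-arm bias is conditional.** A reader might infer that the arm with more dropouts will look structurally better in this trial. The document gives one overall dropout figure and predicts no imbalance. At equal missingness there is no between-arm bias. This stands.
- **The direction is unknown.** A reader might also infer that the rule will hide harm from withdrawing MTX in the Switch group. The document does not support that. Its only arm-specific figures, quoted in the Discussion from MTX-naive patients, show adverse events in 66.1% on filgotinib 200 mg plus MTX and 55.7% on filgotinib 200 mg alone. If these bear on dropout at all, they suggest more of it in the Add-on group. This stands.
- **Other analyses show the films differently.** Item 6 scores dropouts as failures. Change from baseline in mTSS, listed under Other efficacy endpoints, does not score a missing film as non-progression. Structural results as a whole are therefore not hidden, but CRRP and RRP themselves remain understated.
- **Discontinuation films may shrink the problem.** They may, and the steps above ignore them. Mapping such a film to a visit could properly be left to an analysis plan. The numerator and denominator, however, are fixed in item 7, and a plan that follows them keeps the rule.
- **Further sensitivity analyses are promised.** The Discussion does so when describing the missing-at-random assumption of the MMRM, not these proportions.
- **Non-responder might be meant as progressor.** That reading would contradict the explicit item 7 numerator.
- **An evaluable-film denominator can also be biased.** It can, as step 4 shows, so it is not sufficient alone.

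**Conclusion.** The point holds in limited form. Taken literally, item 7 and the general missing-data rule score FAS patients without a week-24 or week-48 film as non-progressors. That is a best-case imputation for a harm endpoint, and the opposite of what item 6 does with the same dropouts. The document states this rule; it is not a detail left out.

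The size is modest. If missingness is unrelated to outcome, both rates are understated in proportion to the missing share: an assumed 10% reads 9.0% at 10% missing. A between-arm bias needs unequal missingness. At 5% versus 15% missing and equal true rates of 10% it is 1.0 point (9.5% versus 8.5%), well inside the sampling error of about 10.7 points. The order of the arms reverses only under the further assumption that dropouts progress more often and are unequally distributed.

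These are secondary endpoints reported as proportions with 95% confidence intervals, with no stated test or margin. The non-inferiority conclusion on DAS28-CRP is unaffected. This should be fixed before the data are analysed, but the trial's main result does not depend on it.

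**What to change.** Four changes to the analysis wording:

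1. Report CRRP and RRP at each visit among patients with a baseline film and an evaluable post-baseline film, and give the number assessed in each arm.
2. State whether and how a discontinuation film is mapped to week 24 or week 48.
3. Because observed cases are themselves biased if dropouts progress more, add a sensitivity analysis that counts missing films as progression or uses multiple imputation of change in mTSS. Multiple imputation needs an exception to the no-imputation statement.
4. Limit the missing-as-non-responder rule in Statistical methods to favourable outcomes.

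The cost is a few sentences and a little more analysis work, with no new data. Reported progression rates will be slightly higher than under the present rule. Making the change before results are known avoids a post hoc choice.

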#### Other efficacy endpoints.

Change from baseline in DAS28-erythrocyte sedimentation rate (ESR), tender joint count, swollen joint count, patient VAS, physician VAS, pain VAS, fatigue VAS, HAQ, CRP, ESR, MMP-3, rheumatoid factor (RF), and mTSS at each time point will be analyzed.

#### Safety endpoints.

Number of cases and incidence rate of adverse events, clinical laboratory values, and vital signs will be recorded from the first dose until week 48 of study treatment initiation. An adverse event is any undesirable symptom, sign, disease, or abnormal clinical laboratory value that occurs in a subject, regardless of whether there is a causal relationship with the study. Worsening of arthritis is considered an insufficient effect of the study treatment and will not be classified as an adverse event. The principal investigator and others will assess the severity of adverse events in three categories (mild, moderate, and severe). The severity of adverse events (mild, moderate, and severe) will be assessed based on the Common Terminology Criteria for Adverse Events (CTCAE). This assessment of severity is different from the evaluation of the seriousness of the adverse event. A serious adverse event is an adverse event that results in death, is life-threatening, requires hospitalization or prolongation of an existing hospitalization, leads to permanent or significant disability or dysfunction, or causes congenital abnormalities in offspring. On the other hand, hospitalizations without adverse events will not be considered serious adverse events if they fall under the following categories:

1) Hospitalizations for purposes other than the treatment or evaluation of an adverse event (e.g., health checkups).2) Hospitalizations for scheduled surgeries or examinations planned before informed consent, provided there is no change in the patient’s condition after initiating the study treatment.3) Hospitalizations required for the administration of the study drug.4) Hospitalizations for the periodic maintenance of pre-existing medical devices (e.g., battery replacements).

Each investigator will make determinations based on these predefined criteria.

All adverse events must be followed up for 28 days after the completion of study treatment or until recovery, whichever comes first. Additionally, serious adverse events must be followed up until they resolve or, if resolution is not expected, until the symptoms stabilize. However, if it is medically determined that follow-up is not necessary, the follow-up for the adverse event may be discontinued.

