Randomized controlled trials comparing the combination of tocilizumab and MTX with a switch to tocilizumab monotherapy in rheumatoid arthritis patients with an inadequate response to MTX have reported a higher incidence of liver dysfunction in the combination therapy group [10,11]. Additionally, long-term MTX use is associated with various complications, such as hepatotoxicity, bone marrow suppression, and lymphoproliferative disorders. Given that filgotinib is effective even without MTX, filgotinib monotherapy is expected to offer a safer treatment option while maintaining efficacy in patients with rheumatoid arthritis who do not respond adequately to MTX. Therefore, we aim to compare the efficacy and safety of filgotinib monotherapy with the combination therapy of filgotinib and MTX in patients with moderate to severe active rheumatoid arthritis who had an inadequate response to MTX.

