## Discussion

The FAITHFUL study protocol outlines a comprehensive investigation into the efficacy and safety of filgotinib monotherapy versus combination therapy with MTX in patients with rheumatoid arthritis who have shown inadequate response to MTX. Such direct comparisons are currently lacking in the literature, as acknowledged in the protocol. Therefore, this study design reflects current challenges in managing rheumatoid arthritis, such as balancing therapeutic efficacy and minimizing adverse effects.

In the FINCH3 trial, the only study comparing filgotinib plus MTX, filgotinib monotherapy, and MTX monotherapy in MTX-naive patients, adverse events up to week 24 were observed in 66.1% (275/416) of patients in the filgotinib 200 mg plus MTX group, 69.6% (144/207) in the filgotinib 100 mg plus MTX group, 55.7% (117/210) in the filgotinib 200 mg monotherapy group, and 63.2% (263/416) in the MTX monotherapy group [9]. Although no statistical tests were conducted, there was a tendency for higher rates in the filgotinib plus MTX groups compared to the filgotinib monotherapy group. Among the major adverse events, the frequency of nausea was 10.3% (43/416) in the filgotinib 200 mg plus MTX group, 15.5% (32/207) in the filgotinib 100 mg plus MTX group, 6.2% (13/210) in the filgotinib 200 mg monotherapy group, and 10.8% (45/416) in the MTX monotherapy group, indicating a trend toward higher rates in the MTX combination groups. Thus, if the FAITHFUL study demonstrates the non-inferiority of filgotinib monotherapy compared to filgotinib plus MTX combination therapy, it could serve as evidence for a treatment approach with equivalent efficacy and fewer adverse effects in the future. This would contribute to establishing a more appropriate treatment strategy for patients with rheumatoid arthritis with insufficient response to MTX.

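### A flare that leads to hospitalisation or lasting disability is neither an adverse event nor a serious adverse event, and no stated endpoint counts such flares by arm

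*Protocol article*

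**What the plan says.** The Safety endpoints section opens with a broad definition: "An adverse event is any undesirable symptom, sign, disease, or abnormal clinical laboratory value that occurs in a subject", whether or not it is causally related. Read alone, this would include a flare of rheumatoid arthritis. The section then takes flares out: "Worsening of arthritis is considered an insufficient effect of the study treatment and will not be classified as an adverse event". No condition on severity, seriousness or hospitalisation is attached.

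Seriousness is defined as a subset: "A serious adverse event is an adverse event that results in death, is life-threatening, requires hospitalization or prolongation of an existing hospitalization", with permanent or significant disability among the further criteria. A list of admissions that are not SAEs follows. Its first item covers admissions for any purpose other than treating or evaluating an AE. Investigators are told to decide by these predefined criteria. Safety data "will be recorded from the first dose until week 48 of study treatment initiation".

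The Introduction says that in patients who do not respond adequately to MTX "filgotinib monotherapy is expected to offer a safer treatment option while maintaining efficacy". The Discussion says that if non-inferiority is shown, "it could serve as evidence for a treatment approach with equivalent efficacy and fewer adverse effects in the future".

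**The concern.** The randomised contrast is whether MTX continues to week 24 (Details of the study treatment). Toxicity of MTX enters the AE tables. A flare after stopping MTX does not, even when it meets a seriousness criterion. If serious flares were more frequent in the Switch arm, the TEAE and SAE tables would not show it, and these are the tables from which fewer adverse effects would be concluded.

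Oversight is affected too. Item 2 of the Study discontinuation criteria starts from a reported SAE. The duty to follow an event until it resolves or stabilises applies to SAEs. As written, neither reaches a serious flare.

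**Working it through.** **Step 1: the definitions.**
- Worsening of arthritis is not an AE (unconditional).
- An SAE is an AE that meets a seriousness criterion.
- So worsening of arthritis is never an SAE, whatever its outcome.
- Item 1 of the hospitalisation list points the same way: an admission for something that is not an AE is not an SAE. It reinforces the gap.

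**Step 2: where worsening is recorded instead.**

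| Place in the article | What it captures | Does it count serious flares? |
|---|---|---|
| Primary endpoint | Mean DAS28-CRP change at week 24 | No |
| Remission, low disease activity, ACR and HAQ rates | Non-achievement, including early discontinuation | No; a hospitalised flare looks like any other non-response |
| Radiographic progression (mTSS increase of 3 or more, 5 or more) | Structural worsening, counted per arm | No; it counts joint damage, not flares |
| Withdrawal criteria | Date and reason of each withdrawal, in the EDC | Only flares that end participation, and no by-arm count is stated |
| Statistical methods | Data up to discontinuation only | A flare that ends participation leaves no later value |

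**Step 3: how far a mean change dilutes a few flares.** Inputs from Sample size calculation and Statistical methods: SD 1.1, 54 evaluable per arm, 90% confidence interval, margin 0.6. Ignoring the baseline adjustment, the largest observed difference that still passes is

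0.6 − 1.645 × 1.1 × √(2/54) = 0.6 − 0.348 = 0.252.

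If k extra Switch patients are each d units worse at week 24, the arm mean moves by k × d / 54. Starting from no other difference, failure needs d above 0.252 × 54 / k. That is 4.5 units each for k = 3 and 2.3 units each for k = 6. Starting from the planned difference of 0.07, failure needs d above 0.182 × 54 / k, which is 3.3 and 1.6 units. These values of k are illustrations. A small excess of serious flares could pass unseen; a larger one might not.

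**Step 4: scale of the AE comparison.** The Discussion cites the earlier trial in MTX-naive patients: "66.1% (275/416) of patients in the filgotinib 200 mg plus MTX group", against 117/210 with filgotinib 200 mg monotherapy.
- 275/416 = 66.1% and 117/210 = 55.7%; both reproduce. The gap is 10.4 points.
- If those rates carried over, 60 × 0.104 ≈ 6 patients per arm.

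**Step 5: range for the missing quantity.** The article gives no flare rate, so both ranges below are assumptions.
- Excess *serious* flares in Switch of 0, 1, 3 or 6 among 60 would leave 0, 1.7, 5.0 or 10.0 points (k/60) out of the SAE comparison.
- If *all* flares counted as AEs, with an excess share f in Switch independent of other AEs, the Switch rate would be 0.557 + 0.443 × f:

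| f | 0% | 5% | 10% | 15% | 20% | 25% |
|---|---|---|---|---|---|---|
| Gap in any-AE rate (points) | 10.4 | 8.2 | 6.0 | 3.7 | 1.5 | −0.7 |

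The gap closes at f = 0.104/0.443 ≈ 23%, or at about 10% if every such flare falls in a patient with no other AE. This second range covers flares of any severity, so it bounds the issue and does not estimate serious flares.

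**The case against.** The strongest reply is that the harm is moved to efficacy and not lost. Treating worsening of the studied disease as lack of effect is a common convention, and counting it as an AE as well would enter the same phenomenon twice. Loss of disease control is what the primary endpoint tests. Responder rates penalise early discontinuation, radiographic progression is counted per arm, withdrawal reasons are recorded, and central monitoring reviews discontinued cases. The rule is the same in both arms, both arms stop biologic and other conventional DMARDs, and only arthritis is excluded. The Discussion makes its safety reading conditional on non-inferiority.

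All of this stands for non-serious worsening, and it is why the proposed change leaves that part of the rule alone. It does not answer the case of a flare that meets a seriousness criterion, which no listed endpoint identifies.

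A reader might infer more than the documents support:
- That flare is the main expected harm of stopping MTX. The article does not say so. It expects efficacy to be maintained and assumes a difference of only 0.07.
- That the safety comparison is biased towards Switch by construction. The rule is identical in both arms; its effect is unequal only if serious flares differ between them.
- That the harm is absent from the trial. It is absent from the AE and SAE tables only.

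Detailed data fields and table layouts may also sit in documents not shown. The unconditional exclusion, however, is stated here.

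**Conclusion.** The point holds in a narrow form. By the article's own definitions, a flare causing admission or lasting disability is neither an AE nor an SAE, cannot reach item 2 of the Study discontinuation criteria, and is not counted by any stated endpoint. If serious flares differ by arm, the AE comparison alone cannot fully support a conclusion of fewer adverse effects.

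The size is unknown; the ranges above rest on assumed rates, and the scale of about six patients per arm assumes that rates from an MTX-naive trial carry over. The primary analysis, margin and sample size are unaffected. This is a cheap correction that should be made, not a threat to the efficacy result.

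**What to change.** 1. Amend the sentence in Safety endpoints so that worsening of arthritis meeting any seriousness criterion is reported as an SAE. Keep non-serious worsening as insufficient effect, outside the AE tables.
2. State that item 1 of the hospitalisation list does not exempt admissions for worsening of arthritis.
3. Beside the TEAE table, tabulate by randomised arm the patients with serious worsening and the withdrawals for worsening. Withdrawal reasons are already entered in the EDC.
4. Show SAE counts with and without worsening of rheumatoid arthritis, and read any statement about fewer adverse effects together with that table.

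The cost is a short protocol amendment, a few more SAE reports and one extra table. No endpoint, sample size or treatment rule changes.
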